Even though continuous aerobic exercise (CAE) seems to produce beneficial effects on depression and associated comorbidities, recent studies have shown that physical exercise with high motor complexity may produce additional benefits to overall health status. Specifically, exercise with high motor complexity may be particularly beneficial for patients with depression as it requires high levels of attention, memory, and motor difficulty, producing greater cortical activation than exercises with low motor complexity (e.g., CAE) [23, 24]. Accordingly, high cortical activity (i.e., due to the integration of perceptual, motor, and cognitive information) has the potential to produce greater neuroplasticity [25] (i.e., changes in brain structure and function) than conditions requiring low cortical activity (low motor complexity). Recent studies from our group demonstrated that 3 months of an exercise program with high motor complexity produced greater cognitive improvement in patients with Parkinson’s disease than exercises with low motor complexity [26]. In addition, hippocampal volume seems to increase after an exercise intervention with high motor complexity (i.e., coordinative exercises) [27]. This finding is particularly important as increases in hippocampal volume are associated with improved brain function, while decreases in hippocampal volume are related to depression symptoms [27].

Taken together, it is reasonable to suggest that high motor complexity aerobic exercises may produce greater health benefits (depression score, cognitive function, hippocampal volume, BDNF expression, sleep parameters, cardiovascular risk parameters, suicidal behavior, functionality and treatment costs) than low motor complexity aerobic exercises (e.g., cycling, running). Thus, we hypothesized that aerobic exercise with motor complexity (AEMC) will be more effective than CAE in improving outcomes of cognitive decline, hippocampal volume, BDNF expression, sleep parameters, cardiovascular risk parameters, suicidal behavior, functionality, and treatment costs in patients with depression undergoing standard drug treatment.

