**Fig. 1 Fig1:**
[figure not shown]
Template of recommended content for the schedule of enrolment, interventions, and assessments

The primary outcome will be the change in the Montgomery-Åsberg Depression Scale (MADRS) score [28]. Secondary outcomes will be (1) cognitive function, assessed by Frontal Assessment Battery score [29], Trail Making Test A and B score [30], Rey’s Auditory-Verbal Learning Test (RAVLT) score [31], Digit Symbol Substitution Test score [32], Montreal Cognitive Assessment (MoCA) score [33], and Stroop test score [34]); (2) hippocampal volume assessed by magnetic resonance imaging (MRI) [35]; (3) BDNF expression [36]; (4) sleep parameters assessed by Pittsburgh Sleep Quality Index score [37], sleep quality assessment by accelerometry and the Biological Rhythms Interview of Assessment in Neuropsychiatry (BRIAN) score [38]; (5) cardiovascular risk assessed by global cardiovascular score, metabolic syndrome, waist circumference, blood pressure, lipid profile (total cholesterol, HDL cholesterol, LDL cholesterol, triglycerides), and glycemia [39, 40]; (6) suicidal ideation and behavior assessed by the Scale Columbia of Suicide score [41] and Scale of Hopelessness score [42]); (7) functionality assessed by gait linear spatial variables [43, 44], Timed Up and Go test (TUG) score [45], TUG cognitive score [46], handgrip strength [47], 6-min walk test [48] physical activity levels (sedentary time, active time, time spent in different physical activity intensities, energy expenditure, and number of steps per day), body weight, and hip and waist circumference [49]; and (8) treatment costs including laboratory procedures, medicines, and doctor consultations per patient [50].

The study will be conducted in accordance with theDeclaration of Helsinki revised in 2008 [51] and approved by the ethics committees of the Department of Health of the city of São Paulo and of the Hospital Israelita Albert Einstein, Certificate of Ethical Appreciation Presentation (PCEA) number 64888017.3.0000.0086. Trial registration is RBR-9zgxzd.

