### Randomization

After baseline assessments, a blind researcher will classify patients into terciles regarding their MADRS score and number of previous depressive episodes. Subsequently, patients from each tercile will be randomly assigned to the control (C), CAE, or AEMC groups. A one-way ANOVA will test for similar initial values for MADRS scores and number of depressive episodes between groups (*P* > 0.05). The Principal Investigator will be blinded to all of the procedures to perform the randomization and analyses.

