### Outcome measures – primary outcome

The MADRS scale [28] encompasses 10 items that assess apparent and reported sadness, inner tension, sleep and appetite changes, concentration difficulties, slowness, inability to feel, and pessimistic and suicidal thoughts. Nine items are based on the patient’s report and one on the psychiatrist’s observations. The higher the score, the greater the presence of depressive symptoms; scores range from 0 to 60 [62]. The MADRS scale will be applied in the pre- and post-intervention assessments.

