### Data analysis and power calculations

The Shapiro–Wilk and Levene’s tests will be used to determine normality and variance equality, respectively. Non-normal data will be log transformed. If the transformation does not produce a normal distribution, the effect of influential points in data analyses will be tested. If influential points change the interpretation of the results, they will be manually removed. Linear mixed models having group and time as fixed factors and patients as a random factor will be performed for each outcome (MADRS, clinical outcomes, hippocampal volume, brain-derived neurotrophic factor, cardiopulmonary parameters, lipid profile, and treatment costs) and domain (especially in clinical outcomes) [85]. In case an outcome presents pre-experimental period differences between groups, determined by a regular one-way ANOVA, an ANCOVA will be implemented having pre-experimental period values as covariates, group as a fixed factor, and patients as a random factor. An intention-to-treat analysis will also be performed in case of a high incidence of missing values, using linear mixed models; the first analysis will be performed removing the missing values, while the second analysis will be performed incorporating the missing data points to determine the impact of missing values in the overall results. Whenever a significant F-value is obtained, a post hoc test with a Tukey’s adjustment will be performed. In addition, within-group (pre- to post-changes) and between-group effect sizes will be calculated using Cohen’s d [86] for each outcome. Effect sizes will be classified as small (≤ 0.49), medium (0.50–0.79), and large (≥ 0.80). Finally, the level of significance adopted in the present study for all analyses will be *P* ≤ 0.05. Data will be presented as mean ± SD. SAS 9.2^®^ software (Institute Inc., Cary, NC, USA) will be used for the statistical analyses described. Considering the importance of the control of the error rates, typical error and coefficient of variation of the assessments will be performed under test and retest conditions in a sub-sample (10 subjects).

For the primary outcome (MADRS) the verification of status of depression (depressed, partial remission, full remission) and the number of patients in remission (< 10 points MADRS) will be verified [14, 87].

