## Discussion

The present study has the objective to verify if patients with depression randomized into one of two physical exercise interventions (AEMC or CAE) combined with traditional drug treatment will present distinct improvements in depression symptoms (MADRS). In addition, different outcomes commonly altered by depression and with the potential to be reversed by physical exercise (e.g., cognitive function, hippocampal volume, brain-derived neurotrophic factor, sleep parameters, cardiovascular risk parameters, suicidal behavior, functionality, and treatment costs) will be evaluated.

From an operational standpoint, a pilot study involving 45 healthy elderly people was carried out in 2017, considering interventions with AEMC (two levels) and CAE (stationary cycling). Data from the pilot study are under analysis, but greater improvements with regards to cognitive and motor aspects were observed in the group undergoing exercises with greater motor complexity. In addition, training interventions produced very high exercise adherence (95%), which may be a differential, considering the difficulties in maintaining adherence during a traditional physical exercise program [89]. The main objective of this pilot study was to establish training routines and assessments and to provide logistical experiences between the parties involved (BHU, University, institutions involved in implementing training interventions and evaluations, and researchers) for the development of the proposal with patients with depression.

To our knowledge, this is the first study to test the effect of adding physical exercise to traditional treatment in patients with depression in a primary health care setting in Brazil. In addition, the use of aerobic exercises with insertion of activities with progressively higher motor complexity has not yet been tested in this population. Considering that exercises with high motor complexity may promote changes in cortical activation [90] and possibly increase the volume of associated encephalic structures (i.e., hippocampus) [27] in healthy individuals, assessing such adaptations in patients with depression is of great interest for clinical practice and public policies.

Finally, determining the impact of physical exercise programs on the treatment costs of patients with depression in Brazil may lead to new polices on how to treat them while decreasing the associated costs [2].

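### As written, the MADRS model names no group-by-time term and lets any significant F open Tukey tests, so no stated test in it targets the AEMC-CAE difference in change

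*Protocol article*

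**What the plan says.** All references are to the protocol article.

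- **Outcome** (Study design): "The primary outcome will be the change in the Montgomery-Åsberg Depression Scale (MADRS) score". It is measured twice (Outcome measures – primary outcome): "The MADRS scale will be applied in the pre- and post-intervention assessments".
- **Question** (Discussion): whether patients "randomized into one of two physical exercise interventions (AEMC or CAE) combined with traditional drug treatment will present distinct improvements in depression symptoms (MADRS". The hypothesis sentence in Background reads "we hypothesized that aerobic exercise with motor complexity (AEMC) will be more effective than CAE in improving outcomes of cognitive decline" and continues through the other secondary outcomes. It leaves out the depression score, although the sentence before it includes that score.
- **Model** (Data analysis and power calculations): "Linear mixed models having group and time as fixed factors and patients as a random factor will be performed for each outcome". No interaction is mentioned here or elsewhere in the article.
- **Gate** (same section): "Whenever a significant F-value is obtained, a post hoc test" with Tukey's adjustment follows. Which F is meant, and which pair of arms matters, is not said.
- **Baseline adjustment** (same section): "In case an outcome presents pre-experimental period differences between groups, determined by a regular one-way ANOVA, an ANCOVA will be implemented", with the baseline value as covariate and group as fixed factor.
- **Allocation** (Randomization): patients are first classed into terciles of MADRS and number of previous episodes, then "patients from each tercile will be randomly assigned to the control (C), CAE, or AEMC groups". A one-way ANOVA is expected to show similar baseline values (P > 0.05).

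**The concern.** With one score before and one after, a treatment effect on change is a group-by-time effect, or equivalently a week-24 group difference given baseline. A model with group and time alone contains neither. The clause that would give a baseline-adjusted comparison applies only after a significant baseline test.

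If the text is followed to the letter, the primary question has no test aimed at it. A real difference between the exercise programmes would probably be missed. A significant time effect, which every arm could produce by improving on medication, would also open the post hoc comparisons. Because neither the F nor the pair is named, several results could later be offered as the primary one.

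**Working it through.** **1. The plan's own figure.** Data analysis and power calculations gives 21 per group from effect size 0.25, power 0.85, alpha 0.05 and correlation 0.8. Assume the effect size is Cohen's f (the metric is not named), with three groups and two times. For a group-by-time F test the noncentrality is f² × N × 2/(1 − ρ). At N = 21 this is 0.0625 × 21 × 2/0.2 = 13.1, and the smallest N reaching 0.85 is 21 in **total**, not per group. So 21 per group is not reproduced. The match of the number is still a hint that an interaction was in mind. The sample size itself is a separate matter.

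**2. What the two F tests estimate.** Let AEMC and CAE have equal means at baseline and differ by d at week 24.
- Group effect in the additive model: difference in the pre/post average = (0 + d)/2 = d/2.
- Time effect: mean change over all arms, with no between-arm information.

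**3. Power for the AEMC-CAE pair.** Assumptions: SD 1 at each time, two-sided 0.05, noncentral t, error df from three arms.
- Additive group effect: estimate d/2, SE = √[((1 + ρ)/2) × (2/n)].
- Week-24 contrast adjusted for baseline: estimate d, SE = √[(1 − ρ²) × (2/n)].

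Example with d = 0.50, n = 25, ρ = 0.8:
- Additive: 0.25/√(0.9 × 0.08) = 0.25/0.268 = 0.93, power 0.15.
- Adjusted: 0.50/√(0.36 × 0.08) = 0.50/0.170 = 2.95, power 0.83.

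| Assumed d (SD), ρ = 0.8 | Additive, 25 per arm | Adjusted, 25 per arm | Additive, 21 per arm | Adjusted, 21 per arm |
|---|---|---|---|---|
| 0.25 | 0.08 | 0.31 | 0.07 | 0.26 |
| 0.50 | 0.15 | 0.83 | 0.13 | 0.76 |
| 0.62 | 0.21 | 0.95 | 0.18 | 0.91 |

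With ρ = 0.5, d = 0.62 and 25 per arm, the values are 0.24 and 0.70.

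The documents give no effect for AEMC versus CAE. The 0.62 in Background is a meta-analytic effect of aerobic exercise on depressive symptoms, and it serves here only as the top of a range.

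**4. Which F opens Tukey.** In simulation (10,000 runs, 25 per arm, ρ = 0.8), all three arms improved by the same 0.5 SD. The time F was significant in 100% of runs, while the group F and an interaction F stayed near 5%. The stated trigger is therefore met with no difference between arms.

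**5. Would the ANCOVA branch apply to MADRS?** Even under simple randomisation, the baseline ANOVA would reach P ≤ 0.05 in only about 5% of trials. With 75 normally distributed baseline scores, terciles of 25 and balanced allocation within each, it did so in 0 of 10,000 simulated trials. This takes the terciles as MADRS terciles. The article does not say how they are combined with the number of episodes.

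**6. If an interaction is intended.** With true changes of 0, 0.25 and 0.5 SD (C, CAE, AEMC), the interaction F was significant in 68% of runs. Tukey on change separated AEMC from CAE in 16%, and a single planned contrast did so in 27%. Naming the primary contrast therefore matters even then.

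**The case against.** The strongest reply is that the sentence lists factors and does not say that the model is additive. A change outcome, a sample size built on a repeated-measures correlation, and the match of 21 with an interaction calculation all suggest that group-by-time was meant, and a condensed article may leave exact model terms to an analysis plan. This stands in part: one cannot conclude that the interaction is excluded, only that it is not stated. But the article does set out the factors, the trigger, the adjustment and the condition for ANCOVA, and what it sets out does not reach the question.

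It is also fair that the ANCOVA branch, followed by Tukey, would compare AEMC with CAE directly. It would, but for MADRS its condition is in practice never met.

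Some stronger readings are tempting and are not supported:
- **A significant three-arm F would itself yield a false AEMC claim.** It would not, because Tukey must still separate the two arms. With changes of 0, 0.5 and 0.5 SD, the interaction F was significant in 81% of runs, but Tukey separated AEMC from CAE in only about 2%.
- **Tukey would run over all six group-by-time cells.** The article does not say this. A difference in change is also not one of the 15 cell pairs, so a six-mean critical value does not apply to it.
- **Comparisons with control must be demoted, or the secondary outcomes relabelled exploratory.** The abstract and Discussion also present adding exercise to drug treatment as a purpose, and the other outcomes are already called secondary. Both are matters of preference.

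**Conclusion.** The point holds for the text as it stands. No test named in the main model targets the AEMC-CAE difference in MADRS change, the trigger for post hoc tests can be met without any arm difference, and the baseline-adjusted alternative is effectively unavailable for the primary outcome.

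The size depends on the literal, additive reading. On that reading, power for the comparison of interest stays at or below 0.21 over the assumed range of 0.25 to 0.62 SD at correlation 0.8, where a properly aimed contrast has 0.31 to 0.95 with the same 25 patients per arm. If an interaction was intended, the power loss from halving the effect disappears. The unnamed F and the unnamed primary pair remain. The omission of depression score from the hypothesis sentence is minor, since other sections make MADRS primary.

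**What to change.** 1. For MADRS, use one of two models in all cases, not conditionally on a baseline test: a week-24 ANCOVA adjusted for baseline MADRS and the randomisation strata, or a mixed model with an explicit group-by-time term from which the contrast in change is taken.
2. Name AEMC minus CAE as a prespecified primary contrast, with the comparisons against control adjusted by Tukey or Holm over the three arms.
3. State that the time and group main-effect F tests neither open post hoc tests nor support an efficacy claim.
4. Add MADRS to the hypothesis sentence in Background.

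The cost is wording. Trial status says that no participant has been included, and the change needs no extra patients, visits or measurements.

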#### Metabolic syndrome

The metabolic syndrome is characterized by the presence of three or more conditions from changes in arterial pressure (systolic pressure ≥ 130 mmHg or diastolic pressure ≥ 85 mmHg), fasting blood glucose (≥ 110 mg/dL), central obesity (abdominal circumference, men > 102 cm and women > 88 cm), dyslipidemia (high LDL-cholesterol, men > 40 mg/dL and women > 50 mg/dL), and triglycerides (> 150 mg/dL) [73].

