#### Clinical outcomes – scales of suicidal ideation, sleep, and BRIAN

The Columbia Suicide Severity rating scale distinguishes suicidal ideation from suicidal behavior. There are four subscales, namely severity of ideation (score of 0–5), intensity of suicidal ideation (score of 0–5), behavior (which is a nominal scale that evaluates actual, aborted, interrupted attempts, and self-injurious behavior, with no intent to commit suicide), and the fourth is the lethality of the actual attempts (scale score 0–6) [41].

The Scale of Hopelessness identifies the level of pessimism, which is directly related to the chance of developing several mental disorders and to suicide risk. The scale consists of 20 true–false questions. The total score is 20 points and each item is scored as 0 or 1 [42].

The Pittsburgh Sleep Quality Index score is a tool widely used for research and practice regarding psychiatric disorders [37]. This questionnaire interprets the perception of sleep quality in a feasible and reliable manner [37, 76]. The overall index is composed of seven components, namely subjective sleep quality (perception of sleep quality of subjects), sleep latency (time between lying on bed and sleeping), duration of sleep (sleeping period reported by the individual), sleep disturbance (sleeping problems), sleep medication (use of sleeping medications), and diurnal dysfunction (daytime sleepiness intensity). All the seven components are scored from 0 (no difficulty for the component of interest) to 3 (very bad). The scores on these components are combined to generate a global score that reflects the sleep quality and disturbances over a 1-month period. The overall score ranges from 0 to 21; if a patient reaches at least 5 points, they are diagnosed with an alteration of sleep. The higher the score the worse the quality of sleep.

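### A linear mixed model is prescribed for every outcome and domain, which takes in a suicidal-behaviour subscale the protocol itself calls nominal and, less harmfully, yes/no metabolic syndrome

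*Protocol article*

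**What the plan says.** The section Data analysis and power calculations names one model: "Linear mixed models having group and time as fixed factors and patients as a random factor will be performed for each outcome", followed by a list in brackets and then "and domain (especially in clinical outcomes". A significant F value leads to Tukey comparisons, Cohen's d is to be computed for each outcome, and data are presented as mean ± SD. For data that fail the normality check, the first remedy is that "Non-normal data will be log transformed". If that does not work, influential points are examined, and they are removed if they alter the interpretation. The fallback for baseline imbalance is an ANCOVA, which is also linear. No logistic, ordinal, multinomial or exact method is named.

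Two secondary outcomes listed under Study design are not numerical:

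- Outcome 6 is "suicidal ideation and behavior assessed by the Scale Columbia of Suicide score". The section on the suicidal ideation, sleep and BRIAN scales, which carries a clinical-outcomes heading, describes one of the four Columbia subscales as "behavior (which is a nominal scale that evaluates actual, aborted, interrupted attempts, and self-injurious behavior".
- Outcome 5 is "cardiovascular risk assessed by global cardiovascular score, metabolic syndrome, waist circumference, blood pressure" and further measures. The Metabolic syndrome section says "The metabolic syndrome is characterized by the presence of three or more conditions", so each patient either has it or does not.

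**The concern.** A linear model compares means. The mean of a nominal variable is a mean of the labels used in the data file, so a different but equally legitimate numbering gives a different mean, a different Cohen's d and a different P value. If the plan is followed as written, whoever numbers the categories can influence the result on suicidal behaviour, which is among the outcomes on which the Background hypothesises that AEMC will do better than CAE.

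For a yes/no outcome the question is different. Numbering cannot matter, but the F test may lose its calibration when events are few, and the planned summaries and transformation do not describe a proportion. This is something the text fixes, not a detail left for later: an analysis plan that follows it inherits the problem, and one that does not would contradict it.

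**Working it through.** **Inputs from the protocol.** Three arms of 25, two assessments, a linear mixed model with an F test, significance at P ≤ 0.05. The protocol gives no frequency for suicidal behaviour and no prevalence for metabolic syndrome in its sample, so those below are assumptions. It states no figure on this point to reproduce.

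**Step 1: one data set, two numberings.** Assume the behaviour subscale is stored as one five-category variable. Assumed counts in the order none / actual / interrupted / aborted / self-injury: arm 1, 20/2/0/1/2; arm 2, 21/0/2/2/0; arm 3, 22/0/1/0/2.

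| Codes (same category order) | Arm 1 mean | Arm 2 mean | Arm 3 mean | One-way F test P |
|---|---|---|---|---|
| 0, 4, 1, 2, 3 | (2×4 + 1×2 + 2×3)/25 = 0.64 | (2×1 + 2×2)/25 = 0.24 | (1×1 + 2×3)/25 = 0.28 | 0.29 |
| 0, 2, 4, 1, 3 | (2×2 + 1×1 + 2×3)/25 = 0.44 | (2×4 + 2×1)/25 = 0.40 | (1×4 + 2×3)/25 = 0.40 | 0.99 |

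The patients are identical; only the labels differ. Over all 5! = 120 numberings, P runs from 0.03 to 0.99. Only 2 of the 120 give P ≤ 0.05, and neither codes no behaviour lowest. Over the 24 numberings that do code it lowest, P runs from 0.29 to 0.99 and none is significant.

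**Step 2: the planned pre/post comparison.** Step 1 uses one time point. With complete data and two assessments, the group-by-time F of a random-intercept model equals a one-way ANOVA of each patient's change. A fitted REML model gave the same P values as that ANOVA under 20 numberings. Null data sets (no true effect) were simulated with assumed category frequencies: either 28% of patients with some behaviour, or 10%. Post-intervention status was either drawn afresh or kept from baseline with probability 0.5.

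- In one such data set, P ran from 0.004 to 0.98 over the 120 numberings, and 18% of numberings gave P ≤ 0.05.
- Over 400 data sets per scenario, the verdict at 0.05 changed with the numbering in 34–41% in three scenarios. It changed in 26% in the fourth (10% frequency with persistence), where some tests could not be computed.
- With no behaviour always coded lowest, a repeat simulation gave about 20% in the most favourable scenario for such changes and about 10% in the least.

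**Step 3: metabolic syndrome and coding.** Replace the codes 0 and 1 by any a and a + b. Every change score is multiplied by b, both sums of squares by b², and F is unchanged. A numerical check gave the same P value (0.245) under three codings.

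**Step 4: metabolic syndrome and error rate.** 20,000 null trials per row. Persistence is the assumed probability that the baseline status is simply kept.

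| Assumed prevalence | Persistence | Type I error (nominal 5%) | Trials with no change in any arm |
|---|---|---|---|
| 2% | 0 / 0.6 / 0.8 | 2.5% / 0.4% / 0.04% | 5% / 30% / 56% |
| 5% | 0 / 0.6 / 0.8 | 5.0% / 2.5% / 0.7% | 0.1% / 5% / 24% |
| 10% | 0 / 0.6 / 0.8 | 4.9% / 4.4% / 2.1% | 0% / 0.4% / 7% |
| 20–50% | 0 to 0.8 | 4.3–5.3% | under 1% |

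The departure is towards too few rejections.

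**Step 5: the transformation.** The log of 0 does not exist. If a constant is added first, two values become two other values, so by Step 3 the test is the same and the data are no nearer to normal. The step cannot achieve its purpose for this outcome.

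**The case against.** The case for leaving the text alone has force in several places.

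- **Metabolic syndrome is not in the bracketed list.** The clinical-outcomes label is used for cognition, suicidality and sleep, function and body composition, not for cardiovascular risk. One could say its method is simply unstated. The words before the bracket still cover every outcome, so the rule reaches it on a literal reading, but less firmly than it reaches the behaviour subscale.
- **The widest P range needs odd numberings.** Most analysts would code no behaviour as 0, and Step 1 then yields no significant result. This stands as a limit on size. It does not remove the problem, because P still moves from 0.29 to 0.99 and verdicts still change in Step 2.
- **Suicidality and cardiovascular risk have other measures**, such as ideation severity and intensity, hopelessness, blood pressure and lipids. This is correct and limits the importance.

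A reader might infer more than the documents support:

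- *That the metabolic syndrome test fails.* This needs a rare condition. The protocol gives no prevalence, enrols patients aged 40 and over who do not exercise regularly, and cites raised odds of the syndrome in depression.
- *That the ordinal ideation and lethality subscales are wrongly analysed.* They are scores, and no harm was shown for them. With an assumed skew on a 0–5 scale, type I error was 4.8% with 60% zeros and 4.5% with 80% zeros.
- *That patients with events would be deleted.* Removal is conditional on a failed transformation and a changed interpretation, so it could happen but is not prescribed.
- *That remission is put through the linear model.* The protocol only asks for the status and the number in remission to be verified.

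**Conclusion.** The point holds for two secondary outcomes, with different weight.

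For the suicidal-behaviour subscale the stated method is wrong on the protocol's own description of the scale. Its means, Cohen's d and P value depend on the numbering. The size depends on assumed frequencies and on storage as one multi-category variable: under no true effect, the 0.05 verdict changes with the numbering in about 26–41% of data sets over all numberings, and in about 10–20% when no behaviour is coded lowest.

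For metabolic syndrome the P value is unaffected by coding. The error rate is near 5% at prevalences of 20% or more, can fall below it at 10% if status is very persistent, and becomes clearly too low only when the condition is rare. What remains is a mismatch of presentation: Cohen's d, mean ± SD and a log transform are not suitable for a proportion.

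The primary MADRS score analysis and the sample size are untouched. The wording should be corrected, but the effect on the trial as a whole is modest.

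**What to change.** Amend Data analysis and power calculations along these lines:

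- Restrict the linear mixed model, Cohen's d and mean ± SD to continuous and score outcomes.
- Analyse suicidal behaviour as any versus none, and tabulate the counts of each behaviour category by arm and visit without a test.
- Analyse metabolic syndrome as present or absent.
- For both, use logistic regression on post-intervention status with group as factor and baseline status as covariate, changing to a Firth-penalised or exact method if events are few. State that trigger in advance.
- Exempt both outcomes from the log-transform and influential-point steps.

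Ordinal or rank methods for the other suicide subscales, and a formal model for remission, are optional and not needed to correct the error.

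The cost is a short paragraph and a little more programming, with no new data. The formal test would say less about the type of behaviour, and patients without a post-intervention assessment would not contribute to it. The change should be made before allocation is revealed to the analysts, so that neither codes nor methods are chosen in view of the results.
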